#### Interim analyses {21b}

There are no planned interim analyses and no planned stopping rules for this trial.

### Plans to give access to the full protocol, participant level-data and statistical code {31c}

This document constitutes the full protocol. Datasets and statistical code used in this study will be available from the corresponding author on reasonable request following completion of the trial.

### Oversight and monitoring

#### Composition of the coordinating Centre and trial steering committee {5d}

The coordinating team will comprise the sponsor and Chief Investigator (based at Hull University Hospitals NHS Trust) and the trial manager, trial coordinators, data management and administrative support (based at York Trials Unit, University of York). The coordinating team will ensure all relevant approvals are in place, will train and support sites to undertake the study and will put measures in place to obtain accurate data. The data management team will process and check data against validation criteria agreed with the trial manager.

The trial management group (TMG) will comprise patient representatives, the sponsor, Chief Investigator, trial manager, trial statisticians, health economists, trial coordinators, co-applicants (clinicians, nurses, researchers) and administrative support staff. The TMG will meet every 2 months to review trial progress and safety.

The Trial Steering Committee (TSC) will comprise an independent chair, three independent members with clinical expertise and two patient representatives. The TSC will meet at least annually to provide overall supervision for the trial on behalf of the sponsor and funder.

#### Composition of the data monitoring committee, its role and reporting structure {21a}

The data monitoring committee (DMC) will comprise a clinician, statistician and nurse, independent of the project team or any institution recruiting for this study.

The DMC will undertake ongoing review of the SWHSI-2 trial’s progress, assessing recruitment, data quality, outcome/efficacy data and safety data. The DMC will meet at least once a year and will make written recommendations with regards continuation of the trial to the TSC.

### Adverse event reporting and harms {22}

For the SWHSI-2 trial, adverse events (AE) will be defined as any untoward medical occurrence experienced by a clinical trial participant, which is temporally associated with study treatment (interventions or control) and is related to the wound or to the study intervention or control treatments.

Adverse events, which might be expected with these wounds, include minor wound infection, cellulitis, oedema, maceration and retention of product in the wound, e.g. wound filler embedding in granulated tissue.

Serious adverse events (SAE) will be defined as any untoward medical occurrence:
Results in deathIs life threateningRequires unplanned inpatient hospitalisation or prolongation of existing inpatients’ hospitalisationResults in persistent or significant disability or incapacityIs a congenital anomaly or birth defectAny other important medical condition that, although not included in the above, may require medical or surgical intervention to prevent one of the outcomes listed

For the purposes of the SWHSI-2 trial, hospitalisation for the treatment of major wound infection, osteomyelitis, wound bleeding, fistulation, for removal of embedded wound filler and for limb amputation, will not be considered a SAE but will be considered and reported as an AE.

Where an adverse event is reported, participating sites will be required to promptly report this to YTU. Where the event is considered serious, causality and expectedness will be confirmed by the Chief Investigator or another clinical member of the SWHSI-2 management team. Where events are unexpected and related these will be reported to the research ethics committee and Sponsor within 15 days.

Adverse and serious adverse events will be routinely reported to the DMC and TSC for their review and oversight.

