NPWT was developed in the 1990s as a treatment for open wounds (although versions for closed wounds are now available they are not the focus here). The device applies a controlled negative pressure (vacuum) to a wound via a specialist dressing, removing wound fluid into a canister [9]. Kinetic Concepts Inc. (KCI), the manufacturer who pioneered the use of NPWT with their V.A.C® device, claim that the mechanical forces generated by the negative pressure create a wound environment that is conducive to healing by removing infective materials and exudate, reducing oedema and promoting perfusion and granulation [10]. NPWT is not anticipated to be used to the point of healing, rather its use is promoted as part of the treatment pathway to reduce the time taken for healing to be achieved.

Despite the increasing use of NPWT as a treatment for SWHSI, there is limited robust evidence to evaluate the effectiveness and cost-effectiveness of this treatment for this patient group. A Cochrane review identified three randomised controlled trials [11–14] of NPWT as a treatment for SWHSI; however, all were small and caution was advised when interpreting the findings [9, 15]. The clinical and cost-effectiveness and the harms and benefits of NPWT in the treatment of SWHSI therefore remain uncertain.

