### Intervention description {11a}

#### Intervention (negative pressure wound therapy — NPWT)

Negative pressure wound therapy (NPWT) devices are used as part of the SWHSI treatment pathway rather than necessarily to the point of healing and are administered by a range of healthcare professionals.

Prior to application of NPWT, the wound is filled with a suitable NPWT-specific dressing (for example, black, polyurethane foam dressings with reticulated (open) pores; white, polyvinyl alcohol foam with high tensile strength, pre-moistened with sterile water; or antimicrobial gauze (impregnated with polyhexamethylene biguanide)). A liner may also be placed in the wound bed to prevent dressing adherence. A controlled negative pressure is then applied to the wound via a specialist vacuum pump dressing. The dressing is attached to tubing, which enables wound fluid to be removed into a canister. The canister is removed and changed weekly or when it becomes full, whichever occurs first.

The device will be used in accordance with manufacturer guidance. The clinical care team, in conjunction with local treatment guidelines, will determine the duration of device use, whether this includes continuous or intermittent pressure cycles, and the type of dressing used. Treatment regimen and details will be recorded during weekly telephone follow-up.

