### Statistical methods

#### Statistical methods for primary and secondary outcomes and additional analyses {20a, 20b}

##### Statistical analysis

Outcome analyses will be conducted following the principles of intention-to-treat with participant’s outcomes analysed according to their original, randomised group. Analysis will be undertaken using Stata version 16 or later (College Station, TX: StataCorp LLC). Significance tests will be two-sided at the 5% significance level, and parameter estimates will be presented with associated 95% CI and *p*-values as appropriate.

Baseline data will be summarised by randomised group, as randomised and as included in the primary analysis [31], using descriptive statistics for continuous variables and count and percentage for categorical variables. No formal statistical comparison of baseline data will be made between the groups.

For the primary outcome of time to healing of the reference wound (derived as the difference in days between randomisation and the first date of complete healing), healing rates will be presented overall and by trial arm. Kaplan–Meier survival curves will be produced for the two groups and the median time to healing with a 95% CI presented. A proportional hazards Cox regression model will be used to compare the healing times between the two groups, adjusting for wound size at baseline, duration of wound in days (time between wound start date and randomisation), and wound location as fixed effects, and centre as a shared frailty effect.

Secondary outcomes, including adverse events, will be analysed where appropriate using regression techniques appropriate for the type of data.

Full details for the statistical analysis will be provided in a statistical analysis plan, which will be prepared prior to the completion of data collection.

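### The adverse event definition depends on an undefined temporal association with treatment, so a strict reading would give the NPWT arm a shorter adverse event window than usual care

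*Protocol article*

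**What the plan says.** Under Adverse event reporting and harms {22}, an adverse event is an untoward occurrence "which is temporally associated with study treatment (interventions or control) and is related to the wound or to the study intervention or control treatments". The two conditions are joined by *and*, so a wound-related event that fails the temporal test is not an adverse event. No window and no lag after stopping treatment are given.

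On treatment length, Background and rationale {6a} says "NPWT is not anticipated to be used to the point of healing". Intervention description {11a} says the devices are "used as part of the SWHSI treatment pathway rather than necessarily to the point of healing", and that the care team "will determine the duration of device use, whether this includes continuous or intermittent pressure cycles, and the type of dressing used". The description of usual care gives no stopping point. Section {11b} has sites record discontinuation of the allocated treatment and any alternative treatment given afterwards.

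On use of the data, the Statistical analysis section says "Secondary outcomes, including adverse events, will be analysed where appropriate using regression techniques" suited to the type of data, within an intention-to-treat framework. Adverse events also go routinely to the DMC and TSC. Section {22} classes hospitalisation for major wound infection, osteomyelitis, wound bleeding, fistulation, removal of embedded filler and limb amputation as adverse events and not as serious ones.

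**The concern.** An adverse event window tied to treatment is harmless when both treatments last equally long. Here they probably do not. Suppose two participants each have a wound infection on day 60 with the wound still open. The usual-care participant is probably still on dressings, so the event counts. If the NPWT participant came off the device some weeks before, a site reading the clause strictly could decide that the event is no longer temporally associated with the intervention and not report it.

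If sites read it that way, adverse events would be ascertained over different periods in the two arms, and the comparison would favour NPWT even with no true difference in harm. Late device harms could also be missed. The section's own list of expected events includes "retention of product in the wound, e.g. wound filler embedding in granulated tissue", which may be discovered only after the device is off.

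The trial is open-label, and section {23} plans no routine on-site audit; the 100% central checks it names cover eligibility and consent. The definition also governs the wound-related hospitalisations that section {22} moves out of the serious category. An analysis plan cannot recover events that sites never reported.

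**Working it through.** The protocol states no adverse event rate that could be reproduced, so the check has two parts: what the text fixes, and how far the two readings can diverge.

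**1. The two readings**

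- *Strict:* study treatment in the NPWT arm means the device and its dressings, as {11a} describes them. Later dressings are alternative treatment in the sense of {11b}. The window closes at, or soon after, removal of the device.
- *Broad:* study treatment means the whole allocated pathway, or the association means any time after treatment has begun. The window is then the same in both arms.

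Nothing in the protocol selects one. The broad reading leaves the temporal clause excluding almost nothing; the strict reading gives it force but makes the windows unequal.

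**2. Size of the gap under the strict reading**

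Inputs from the protocol: median healing 86 days (usual care) and 65 days (NPWT), and 12-month follow-up, from Sample size {14}; cohort infection risk 32.1%, from {6a}.

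Assumptions not in the protocol: exponential healing; a constant infection hazard *h* while the wound is open, equal in both arms; the 32.1% applying to open-wound time over 365 days; control dressings continuing to healing; nothing counted after NPWT stops; and NPWT use of W = 14, 28 or 42 days.

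Healing rates: ln 2/86 = 0.00806 per day (control) and ln 2/65 = 0.01066 per day (NPWT).

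Risk of infection while the wound is open and within W days, with healing rate r:

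P(W) = h/(h + r) × [1 − exp(−(h + r)W)]

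Setting P(365) = 0.321 with r = 0.00806 gives h = 0.00388 per day. In the NPWT arm h + r = 0.01455 and h/(h + r) = 0.267.

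| Window in NPWT arm | Recorded infection, NPWT | Usual care | Apparent risk ratio |
|---|---|---|---|
| 14 days | 4.9% | 32.1% | 0.15 |
| 28 days | 8.9% | 32.1% | 0.28 |
| 42 days | 12.2% | 32.1% | 0.38 |
| 365 days (common window) | 26.6% | 32.1% | 0.83 |

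The 0.83 is not an ascertainment artefact. It reflects less open-wound time if NPWT shortens healing to 65 days. If healing is the same in both arms, the common-window ratio is 1.0.

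**3. The same check with no treatment effect at all**

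With a median of 86 days in both arms and a constant event rate while the wound is open, expected event counts are proportional to counted open-wound days, (1 − exp(−rW))/r. Over 365 days this is 117.5. For W = 7, 14, 28 and 42 it is 6.8, 13.2, 25.1 and 35.6. The apparent ratios are 0.06, 0.11, 0.21 and 0.30, against a true ratio of 1.0. They are lower than those in the table because they count all events and not only first infections.

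Under the broad reading every row reverts to the common-window result.

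**The case against.** The strongest reply is that the on-device reading belongs to the reader and not to the protocol. The clause does not say that events count only while NPWT is in use. Several points support this reply.

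- Section {22} lists embedded filler as an expected event, and reports hospitalisation for its removal as an adverse event with no on-device condition. A strict reading sits badly with that.
- Section {18a} has weekly calls asking about adverse events in the same way in both arms, whatever the treatment status.
- Section {12} collects antibiotics, admission, re-operation, amputation and death from the weekly calls, and wound infection by questionnaire at 3, 6 and 12 months and at the healing visit. Section {18a} adds a CDC-criteria infection assessment at that visit, covering the time since the wound was open. None of these carries the temporal clause, and the serious adverse event definition does not repeat it.
- The protocol says only that NPWT is not expected, or not necessarily used, to healing. It does not say that it stops long before healing, it gives no duration, and it does not state that usual-care dressings continue to healing.

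All of this stands, and it limits the point. A reader might infer that later wound harms do drop out of the NPWT arm, or that infection would be compared unfairly. The documents support neither: the first needs one particular reading of an undefined phrase, and infection is a secondary outcome measured at the same times in both arms.

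What the reply does not remove is the ambiguity. The weekly calls ask about adverse events, but this definition determines what counts as one. Oedema, maceration, retained filler, wound bleeding and fistulation are not named among the secondary clinical events. Section {31c} describes the article as the full protocol, so the definition cannot be assumed to be completed elsewhere.

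**Conclusion.** The point holds as a conditional one. The definition ties adverse events to an undefined temporal association with treatments that probably differ in length. A strict reading would shorten the NPWT window and favour NPWT; a broad reading would not. Bias is possible but not shown.

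Its reach is the adverse event tabulation, the between-arm regression based on it, and the adverse event reports to the DMC and TSC. The primary outcome and the separately collected clinical events and infection measures are unaffected.

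The apparent ratios of 0.15 to 0.38 for infection, and 0.06 to 0.30 for all wound events with equal healing, are worst cases. They require strict counting at every site, no capture after device removal, a constant hazard and NPWT durations that the protocol does not give. Any distortion shrinks as more sites read the clause broadly. This is a cheap improvement worth making, not a demonstrated flaw in the harms comparison.

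**What to change.** Replace the temporal clause with a window fixed by randomisation and identical in both arms. An adverse event would be any untoward medical occurrence between randomisation and 12 months that is related to the reference wound or to any treatment applied to it, whether or not the allocated treatment is still in use. Optionally, have sites record whether NPWT was in use at onset, so that on-device events can be described as a secondary summary. Check weekly call forms already returned against the new wording.

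The cost is a wording amendment, a note to sites and, if wanted, one tick-box. The weekly calls already ask about adverse events. The downside is some additional adverse event forms and a retrospective check for those already recruited, 252 of 696 at the time of the article. The other 444 (63.8% of the target) would be covered from the start if the change were made then.

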### Frequency and plans for auditing trial conduct {23}

No on site auditing of trial conduct will be completed, unless circumstances prevail (e.g. serious breach of GCP) that warrant this. Centralised monitoring checks of eligibility and consent will be completed for 100% of participants and an annual audit of site files and documentation, via a self-complete checklist, will be completed with each participating NHS Trust. Further details relating to these activities will be documented in a study specific monitoring plan.

The TMG will meet very two months to continuously evaluate the conduct of the study, in addition to routine review by the independent DMC and TSC.

### Plans for communicating important protocol amendments to relevant parties (e.g. trial participants, ethical committees) {25}

Any protocol amendments will be approved by the Sponsor (Hull University Hospitals NHS Trust) and the Funder (NIHR Health Technology Assessment Programme) prior to submission to the approving Research Ethics Committee (Yorkshire and Humber Leeds East) and the Health Research Authority. Documentation will be provided to study sites for their local review and implementation as required.

### Dissemination plans {31a}

Following completion of the SWHSI-2 Trial, irrespective of the magnitude of effect, we will submit the study results to peer reviewed journals. The executive summary and trial report will also be sent to the National Institute for Health and Care Excellence (NICE) and other relevant bodies, including Clinical Commissioning Groups, to facilitate translation into clinical practice.

We will produce a plain English summary of the report and disseminate this to participants, members of our patient advisory group and relevant patient-focused websites. Patient information will also be generated for “Shared Decision Making”, the entry on Wikipedia and the Map of Medicine entry.

## Discussion

Use of NPWT as a treatment for SWHSI has been rapidly increasing despite there being limited high-quality evidence to support its clinical and cost-effectiveness. Given the increasing use of this device in routine care, a full and sufficiently powered randomised controlled trial is essential to evaluate the effectiveness of this treatment for SWHSI. The SWHSI-2 trial is therefore designed to generate robust evidence to fill this gap.

### Study status

Recruitment to the SWHSI-2 Trial commenced in May 2019, and to date 252 participants of the target 696 (36.2%) have been recruited. Twenty sites are currently open to study recruitment, with recruitment of at least one participant having occurred at 18 sites to date.

The impacts of the COVID-19 pandemic resulted in a pause of recruitment between 23 March and 29 July 2020. Subsequent waves of COVID-19, including the presence of new variants across the UK, have limited the study’s ability to recruit to target due to substantial reductions in elective surgeries across the NHS, due to staff sickness and/or isolation, and the requirement of NHS Trusts to prioritise urgent public health studies in relation to COVID-19. Recruitment activity will therefore continue to ensure sufficient recruitment to enable a powered analysis.

Despite COVID-19, attrition remains low within the study. Use of a clinical, rather than patient-reported, primary outcome (time to wound healing in days since randomisation) has enabled collection of primary outcome data from treating healthcare professionals, if required and subject to participant consent, which has reduced any potential attrition for this key outcome. Follow-up assessment of participants through use of telephone and video assessments, conducted by the coordinating team when required, has been used throughout to minimise attrition for secondary outcomes.

Results of the SWHSI-2 study are currently expected in 2022.

## Abbreviations

AE: Adverse event
BMI: Body mass index
CACE: Complier average causal effect
CDC: Centre for Disease Control
CI: Confidence interval
CRF: Case report form
DMC: Data monitoring committee
EQ-5D-5L: EuroQol 5 Domain 5 Level
GCP: Good clinical practice
ID: Identification
KCI: Kinetic Concepts Inc.
MRC: Medical Research Council
MUST: Malnutritional universal screening tool
NHS: National Health Service
NICE: National Institute for Health and Care Excellence
NIHR: National Institute for Health Research
NPWT: Negative pressure wound therapy
PIS: Participant information sheet
QALY: Quality adjusted life year
SAE: Serious adverse event
SWAT: Study within a trial
SWHSI: Surgical wound healing by secondary intention
TMG: Trial management group
TSC: Trial steering committee
WHQ: Wound Healing Questionnaire
YTU: York Trials Unit
